#### **Subgroup analyses:**

Pre-specified subgroups defined by the following parameters will be analyzed by the trial statistician:

1. Daily glucocorticoid dose (in mg prednisone-equivalent) at the time of inclusion
2. Cumulative glucocorticoid dose (in mg prednisone-equivalent) in the 28 days prior to inclusion
3. Sex
4. Concomitant immunosuppressive drugs at inclusion or during follow-up
5. Underlying disorder
6. Result of the 250 mcg synacthen® test

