### 3.7 Risks / Benefits

Potential risks:

In the standard treatment (prednisone) arm, the potential risks are those of unwarranted and prolonged glucocorticoid therapy, in particular: weight gain, osteopenia/osteoporosis, hyperglycemia, hypertension, muscle catabolism, increased susceptibility to infections due to immunosuppression, and suppression of the endogenous cortisol production by the adrenals.

In the intervention (placebo) arm, there is a potential risk of flare-up of the inflammatory disorder (although this is not based by high-grade evidence), and of unforeseen glucocorticoid requirements, be it due to flare-up of the underlying disease, glucocorticoid deficiency, or glucocorticoid withdrawal syndrome. The risk of endangering the patients is offset by the ease of glucocorticoid stress prophylaxis and cover in case of signs and symptoms of hypocortisolism, for which patients will be instructed and provided with an emergency dose of five 10 mg tablets of prednisone.

Trial participants in both treatment arms may be at risk for severe courses of coronavirus disease-19 (COVID-19), be it due to immunosuppression following longstanding glucocorticoid treatment prior to study enrolment, or due to iatrogenic hypocortisolism, or both. While COVID-19 vaccination is not mandatory for trial participation, patients should be encouraged to undergo vaccination. All participants are carefully instructed regarding emergency glucocorticoid therapy. This so-called stress prophylaxis should also be taken by the patient should post-vaccination symptoms of viral disease occur, but not routinely in order not to jeopardize efficacy of the vaccine. The “TOASST” trial will be conducted in accordance with all current instructions by the competent authorities.

Potential benefits:

The main overall benefit of this trial is the generation of high-level evidence about the feasibility and safety of rapid glucocorticoid withdrawal in comparison with a tapering regime, as no published data on this topic exists from randomized controlled trials.

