## **8.2 Administration of experimental and control interventions**

### **8.2.1 Experimental Intervention**

Prednisone and other synthetic glucocorticoids are administered in a variety of inflammatory and autoimmune disorders. For most of these, there are no dose regimens that were established in randomized controlled trials, e.g. by head-to-head comparisons. In this trial, therapy of the underlying disease is entirely at the discretion of the treating physician. This includes the decision that the disease is stable and the glucocorticoid is administered at a daily dose that warrants its termination. Our hypothesis that abrupt glucocorticoid stop will not be inferior to tapering, with respect to clinical outcome, can only be tested in a randomized, placebo-controlled trial. Hence we chose placebo as comparator in the experimental arm.

The experimental intervention consists of oral administration of placebo tablets matching those filled with prednisone for 4 weeks. Follow-up is for 6 months after enrolment.

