### **8.3 Dose modifications**

The decision to start unplanned open-label glucocorticoid therapy during the blinded treatment phase or during follow-up rests with the treating physician or the patient, not the study team. Indication to do so include flare-up of the underlying disease, symptoms and signs of cortisol deficiency such as weakness, apathy, nausea, vomiting, abdominal pain, hyperthermia, hyponatremia, hyperkalemia, hypoglycemia, or adrenal crisis (i.e. glucocorticoid-responsive shock) (see also section 8.6. below). Should the study physician suspect the necessity of open-label glucocorticoid therapy during follow-up, he/she will contact the treating physician to prompt a visit.

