### **8.7 Concomitant Interventions (treatments)**

Any concomitant care or/and intervention is at the discretion of the treating physician and will be recorded on the CRF. If such care/intervention leads to hospitalization, it will affect the trial as component of the primary as well as one of the secondary outcomes. Any concomitant care and interventions will be recorded in the CRF.

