### 11.2 Determination of Sample Size

To assess the primary outcome measure, a Cox proportional hazards regression model will be fitted to the data. Non-inferiority will be concluded if the two-sided 95% confidence interval of the hazard ratio between the experimental and the control arm lies entirely below the critical hazard ratio defined as

$$HR = \frac{\lambda_e}{\lambda_c} = \frac{\frac{-\log(\pi_{et})}{t}}{\frac{-\log(\pi_{ct})}{t}} = \frac{\log(\pi_{et})}{\log(\pi_{ct})} = \frac{\log(\pi_{ct} - m)}{\log(\pi_{ct})}$$

where  $\lambda_e$  and  $\lambda_c$  are the hazard rates in the experimental and control arms,  $t$  is a fixed point of time,  $\pi_{et}$  and  $\pi_{ct}$  are the proportions of event-free patients at time  $t$ , and  $m$  is the non-inferiority margin expressed as the additional proportion of patients having had an event in the experimental arm, assuming that the occurrence of events follows an exponential distribution. Noninferiority will be concluded if the upper limit of the two-sided 95% confidence interval of the hazard ratio lies below the critical hazard ratio.

For the sample size estimation, the following assumptions were made:

- Patients are randomized to the control and experimental arms in a 1:1 ratio.
- After inclusion, all patients are followed for 6 months. Patients without an event within 6 months are considered right-censored and are not followed any further even though the trial might be ongoing.
- 10% of patients drop out within the 6 months follow-up period. The drop-out events are distributed uniformly over this period.
- The event rate within the 6 months follow-up period, i.e., the proportion of patients with an event, is 40%, both for the control and the experimental arms. We estimated this overall figure based on expected relapse rates for the various eligible diseases, as indicated by clinical experts and published data, e.g. in COPD or inflammatory bowel disease. Our estimation is conservative since the other components of the combined primary outcome will contribute to the event rate.
- The survival curves in the control and experimental arms follow the same exponential distribution. The rate parameter of the exponential distribution is chosen so that the corresponding cumulative distribution function value at 6 months equals the assumed event rate.

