- The non-inferiority margin is defined as an absolute increase of the event rate by 13% over 6 months. We used a modified Delphi approach to determine this margin. 10 experienced clinicians board-certified in internal medicine and/or rheumatology, gastroenterology, and endocrinology were individually asked to define the maximum increase in outcome events they would accept for the benefit of rapid glucocorticoid stop and gain of high-quality scientific data in the area of steroid withdrawal. Assuming an event rate of 40% in the standard treatment arm, the mean tolerable increase under experimental treatment was 13.6% (range, 5 to 20%; median, 13%).
- The significance level is 5%.

For each combination of the noninferiority margins 7.5%, 7.6%, ..., 17.5%, and the sample sizes  $n = 200, 210, \dots, 1200, 999$  individual data sets were simulated based on the above assumptions. A Cox proportional hazards regression model was fitted to each data set, and the hazard ratios for the experimental vs. the control arm with the associated 95% confidence interval were estimated. Noninferiority was concluded if the upper limit of the two-sided 95% confidence interval of the hazard ratio was below the critical hazard ratio (see above equation). The power was estimated as the proportion of positive conclusions divided by the total number of the 999 iterations per parameter combination. To achieve a power of 80%, 573 patients (95% CI, 565 to 580) need to be included, assuming an event rate of 40% over the 6 months follow-up period and setting the non-inferiority margin to 13% (Figure). The critical hazard ratio for this noninferiority scenario is 1.478.

The sample size of  $n=573$  is a conservative estimation, since the assumed drop-out rate of 10% is relatively high.

[figure not shown]

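### Subgroup 4 counts immunosuppressive drugs given during follow-up, so membership can depend on post-randomisation events and the within-subgroup hazard ratios can be biased

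*Protocol*

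**What the plan says.** Under the subgroup heading of section 11.4.3 the protocol announces: "Pre-specified subgroups defined by the following parameters will be analyzed by the trial statistician". The fourth of six items reads "Concomitant immunosuppressive drugs at inclusion or during follow-up". The daily dose and the prior cumulative dose are tied to inclusion, sex and underlying disorder precede randomisation, and the ACTH test is done in every participant on day 1. Only item 4 expressly reaches into follow-up. Nothing in the protocol limits it to use before the primary event or treats it as a time-dependent exposure.

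Other sections bear on how a patient could come to such a drug after randomisation:

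- Section 8.2.1: "therapy of the underlying disease is entirely at the discretion of the treating physician".
- Section 8.7: "Any concomitant care or/and intervention is at the discretion of the treating physician and will be recorded on the CRF".
- Section 8.3, on open-label glucocorticoids, whose unplanned start is a component of the primary outcome: "Indication to do so include flare-up of the underlying disease".
- Section 11.2, on the 40% event rate: "We estimated this overall figure based on expected relapse rates for the various eligible diseases".
- Section 3.7, on the abrupt-stop arm: "there is a potential risk of flare-up of the inflammatory disorder".

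The visit schedule in section 9.1 collects concomitant therapy on day 1 and at every later contact up to day 180.

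**The concern.** A subgroup analysis compares the arms within each category. Randomisation protects that comparison only if the category is fixed by facts that treatment cannot influence. On the natural reading of item 4, a patient who takes no immunosuppressive drug at inclusion, relapses, and is then given one moves from non-user to user. The same relapse may already have produced the primary event. Users are then enriched with events and non-users depleted of them. If the arms truly differ in event risk, enrichment and depletion also differ by arm, and the hazard ratios in the two categories drift apart although the drugs modify nothing.

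At stake is the reading of one secondary analysis: whether abrupt stopping does better or worse in patients with other immunosuppression. As defined, an apparent interaction could be an artefact of classification. More patients would not remove it.

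**Working it through.** **1. The plan's own figure.** With 60% of controls event-free at 6 months and a margin of 13 percentage points (section 11.2), the critical hazard ratio is log(0.60 − 0.13)/log(0.60) = log(0.47)/log(0.60) = 1.478. This matches the protocol. It serves below as a true effect that is equal in all patients.

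**2. Assumptions not in the protocol.**

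- b, share on such drugs at inclusion: 20% or 40%.
- s, share of patients with an event who start one: 30% or 50%.
- q, share of event-free patients who start one: 3%.
- The drugs have no effect on the event or on the treatment effect.

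**3. Formulas.** In an arm with 6-month event risk p:

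- users' risk = p[b + (1−b)s] / { p[b + (1−b)s] + (1−p)[b + (1−b)q] }
- non-users' risk = p(1−s) / { p(1−s) + (1−p)(1−q) }
- subgroup HR = log(1 − risk, abrupt stop) / log(1 − risk, taper)

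**4. One case by hand** (b = 0.20, s = 0.50, q = 0.03, drop-out ignored; p = 0.40 on taper, 0.53 on abrupt stop).

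- Users, taper: 0.40 × 0.60 = 0.240; 0.60 × 0.224 = 0.1344; risk 0.240/0.3744 = 0.641.
- Users, abrupt stop: 0.53 × 0.60 = 0.318; 0.47 × 0.224 = 0.1053; risk 0.318/0.4233 = 0.751.
- HR in users = log(0.249)/log(0.359) = 1.36.
- Non-users, taper: 0.40 × 0.50 = 0.200; 0.60 × 0.97 = 0.582; risk 0.200/0.782 = 0.256.
- Non-users, abrupt stop: 0.53 × 0.50 = 0.265; 0.47 × 0.97 = 0.4559; risk 0.265/0.7209 = 0.368.
- HR in non-users = log(0.632)/log(0.744) = 1.55.

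**5. The range.** Cox models were fitted to simulated trials of 400,000 patients on the protocol's event model (exponential times, 40% events at 6 months on taper, 10% uniform drop-out).

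| True HR | Start rate after an event | HR, users (item 4) | HR, non-users (item 4) |
|---|---|---|---|
| 1.478 | equal by arm (30% or 50%) | 1.35–1.44 | 1.51–1.56 |
| 1.00 | equal by arm (30% or 50%) | about 1.00 | about 1.00 |
| 1.00 | 30% taper, 50% abrupt stop | 1.14–1.20 | 0.75 |
| 1.00 | 50% taper, 30% abrupt stop | 0.82–0.89 | 1.33–1.34 |

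In the second row the hazard ratios are sound, but taper-arm event rates are 46% to 63% in users and 24% to 31% in non-users, against 38% overall after drop-out.

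**6. With the subgroup fixed at inclusion.** The same simulations give 1.46 to 1.51 when the truth is 1.478 and 0.98 to 1.02 when it is 1.00, so the truth is recovered within simulation error.

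**7. Size against noise.** Take the case in step 4, the widest of the equal-start cases, with about 286 patients per arm. Users have 286 × 0.60 × (0.40 + 0.53) ≈ 160 events. Non-users have 286 × 0.80 × 0.50 × (0.40 + 0.53) ≈ 106. The standard error of the difference in log HR is about √(4/160 + 4/106) = 0.25. The spurious difference from the simulation is ln(1.563/1.353) = 0.144, about 0.6 standard errors.

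**The case against.** Four points can fairly be made for the plan.

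- **The bias is conditional.** With no true difference between the arms and equal start rates, the hazard ratio stays near 1 in both categories. This stands. A reader might infer that the subgroup effects must be biased; step 5 does not support that.
- **The equal-start distortion is modest.** At this trial's size it lies well within sampling error, as step 7 shows. This stands. The larger distortions need start rates that differ by arm. Section 6.2.2 blinds participants, treating physicians and outcome assessors, which makes such a difference less likely, although section 6.3 allows unblinding where treatment requires it.
- **The link is inferred.** The protocol nowhere says that relapse leads to immunosuppressive drugs, and it gives no start rates. This also stands. The inference is sound, because treatment of the underlying disease is left to the physician and the expected event rate is built on relapse.
- **The classification could be refined in the analysis plan.** Section 11.4 defers detailed methods to a document not at hand, and separate baseline and follow-up classifications are not excluded. But the protocol itself states the definition, and its natural reading combines the two periods.

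Blinding does not answer the first row of the table: when the arms truly differ, equal start rates are enough to separate the two hazard ratios.

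**Conclusion.** The point holds in a limited form. Item 4 lets post-randomisation events decide subgroup membership, so its arm comparisons are not protected by randomisation and can be biased. Under the assumed ranges, a uniform hazard ratio of 1.478 would appear as about 1.35 to 1.44 in users and 1.51 to 1.56 in non-users. Size and direction rest on start rates that the protocol does not give.

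Two stronger readings are not supported. A reader might take the gap in event rates between users and non-users for a treatment effect. It is a contrast between categories that appears in both arms alike, and it coexists with hazard ratios near 1 when the arms do not differ. A reader might also infer that the trial's main conclusion is at risk. The primary Cox analysis, the critical value of 1.478 and the sample size of 573 do not use this subgroup.

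**What to change.** In section 11.4.3, end item 4 after the word *inclusion*, so that the subgroup rests on immunosuppressive drugs in use at inclusion only. Report drugs started during follow-up descriptively by arm, outside the subgroup analyses.

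The cost is the deletion of three words and one descriptive table. Concomitant therapy is already recorded on day 1 and at each later contact, so no new data are needed and the sample size does not change. Sections 11.4 and 11.4.6 already provide for documenting such a change, which should be made before database closure.

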#### **11.4.4 Interim analyses**

Once 70% of the planned sample size will have their primary endpoint assessed, we will perform a blinded, pooled, sample size re-estimation. To this end, the global rate of events – pooled over both treatment arms – will be calculated, and compared to the assumed rate in the sample size estimation. The sample size estimation will be repeated as performed originally and the study's sample size adjusted accordingly in case more patients are needed. In no case will the originally calculated sample size be reduced.

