#### 11.4.2 Primary Analysis

A Cox proportional hazards regression model with time to the (combined) primary endpoint as the response and treatment arm as the explanatory variable will be fitted, stratified after study centre, prednisone dose, and age group. Non-inferiority will be concluded if the two-sided 95% confidence interval of the hazard ratio (HR) between the experimental and the control arm lies entirely below the critical HR ratio of 1.478. The analysis will be conducted on the PP set.

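### Read literally, the blinded sample size re-estimation re-derives the critical HR from the 13-point margin and so would not materially raise N, while the primary test stays at HR 1.478 and loses power if events fall below 40%

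*Protocol*

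**What the plan says.** Section 11.2 starts from an absolute margin: "The non-inferiority margin is defined as an absolute increase of the event rate by 13% over 6 months". It converts this to a critical hazard ratio by an equation in the control event-free proportion and the margin, and each simulated trial was judged against that equation. For the planning scenario (40% event rate in both arms) the result is 1.478 and "To achieve a power of 80%, 573 patients (95% CI, 565 to 580) need to be included".

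Section 11.4.2 takes the planning value as a constant. Non-inferiority is concluded if the confidence interval of the hazard ratio "lies entirely below the critical HR ratio of 1.478". Nothing provides for updating it.

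Section 11.4.4 compares the blinded pooled event rate with the assumed rate once 70% of the planned sample has the primary endpoint assessed. Then "The sample size estimation will be repeated as performed originally". N may go up but not down. The section does not say whether the critical hazard ratio is kept at 1.478 or derived again.

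**The concern.** A blinded, increase-only re-estimation protects power when events are rarer than planned. It can do so only if it sizes the test that will be performed.

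A literal repeat of section 11.2 puts the new event rate into the critical-HR equation as well as into the expected event count. With a fixed 13-point margin, a lower event rate gives a wider critical HR. The two effects nearly cancel, so the look finds no need for more patients. The test in 11.4.2 gets no wider limit, so it bears the full loss of events. The trial could pass its look, finish at 573 and be inconclusive for want of events.

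**Working it through.** **Inputs (Protocol 11.2).** Two-sided 5% level; 80% power; 1:1 allocation; true HR of 1; 40% event rate over 6 months in both arms; 13-point margin; "10% of patients drop out within the 6 months follow-up period", spread uniformly over that period.

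**Formulas.** For event rate p:
- Critical HR = ln(1 − p − 0.13) / ln(1 − p).
- Events for 80% power (Schoenfeld) = 4 × (1.960 + 0.8416)² / (ln HR)².
- Probability of an observed event per randomised patient, under two treatments of drop-out:
  - (a) drop-outs give no information: 0.9p.
  - (b) drop-out times are uniform: 0.9p + 0.1 × [1 − p/λ], with λ = −ln(1 − p).
- N = events / probability.
- Power = Φ(½ × √events × ln 1.478 − 1.960).

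**Reproducing the plan at p = 40%.**
- Critical HR = ln 0.47 / ln 0.60 = 1.478, as stated.
- Events = 31.40 / 0.3907² = 205.7.
- N under (a) = 205.7 / 0.36 = 571, against 573 (565 to 580) stated.
- N under (b) = 205.7 / 0.3817 = 539, so 573 has about 82% power.

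Treatment (a) reproduces the stated figure. Treatment (b) is what the text describes. Both are carried below.

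**Repeating the method at p = 30%.** Critical HR = ln 0.57 / ln 0.70 = 1.576. Events = 31.40 / 0.4549² = 151.7. N under (a) = 151.7 / 0.27 = 562, which is below 573.

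**The fixed rule at p = 30%, N = 573.** Under (a), events = 573 × 0.27 = 155, and power = Φ(½ × √154.7 × 0.3907 − 1.960) = Φ(0.47) = 68%. Under (b), events = 164 and power = 71%. For 80% power at 1.478, N = 205.7 / 0.27 = 762 under (a) and 719 under (b).

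| Event rate | Re-derived HR | N if re-derived, (a) / (b) | Power of the 1.478 rule at 573, (a) to (b) | N for 80% at 1.478, (a) / (b) |
|---|---|---|---|---|
| 20% | 1.795 | 510 / 482 | 51-53% | 1143 / 1080 |
| 25% | 1.662 | 541 / 511 | 60-63% | 914 / 864 |
| 30% | 1.576 | 562 / 531 | 68-71% | 762 / 719 |
| 35% | 1.518 | 572 / 540 | 75-77% | 653 / 616 |
| 37% | 1.500 | 573 / 541 | 77-79% | 618 / 583 |
| 40% | 1.478 | 571 / 539 | 80-82% | 571 / 539 |
| 50% | 1.434 | 536 / 505 | 88-90% | 457 / 430 |

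The re-derived N peaks near a 37% event rate, at 573.1 under (a) and 540.7 under (b). That is about 2 patients above its value at 40% in either case.

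**Simulation check.** Cox models fitted at N = 573 with uniform drop-out gave power against 1.478 of 76%, 70% and 63% at event rates of 35%, 30% and 25%. Against the re-derived HR the same settings gave 82%, 82% and 84%. A repeat of the original calculation would therefore not show the shortfall.

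**The case against.** The strongest objection is that 11.4.4 does not say what happens to the critical HR. If the sponsor means to hold 1.478, the look does raise N, to 719-762 at a 30% rate. The literal reading also leaves the provision for more patients with almost nothing to do, and the SAP, which is not shown, may settle the matter. This stands in part: the finding is conditional on the literal reading. That reading is still the more natural one, because 11.2 describes judging each simulated trial against the equation, and the protocol itself fixes both the method of the repeat and the threshold of the test.

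A reader might infer that the re-estimation can never return a larger number. The documents do not support so flat a statement. The original result came from 999 simulated data sets per scenario, with an interval of 565 to 580, so noise could add a few patients. The 573 peak also depends on treatment (a); with the stated uniform drop-out the peak is 541.

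A reader might also infer that the protocol leaves open whether 13 points or 1.478 decides the trial. It does not. The synopsis, 11.2 and 11.4.2 all decide on the hazard ratio, 11.4.2 fixes the value, and no risk-difference test is planned. The 13 points are the input from which 1.478 was derived.

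Finally, 11.2 calls the 40% rate conservative, because other components of the composite add events. No figure in the protocol points to 20-25%, so the lower rows are scenarios and not forecasts. At 35% the loss is modest.

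**Conclusion.** The concern holds as a mismatch between 11.4.4 and 11.4.2; no stated number is wrong. On the literal reading, the re-estimation returns an N that does not materially exceed 573 at any event rate. The power of the actual test at 573 meanwhile falls to about 75-77% at a 35% event rate, 68-71% at 30% and 60-63% at 25%. The shortfall against 80% power is 43-80 patients at 35% (616-653 less 573), 146-189 at 30% and 291-341 at 25%.

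The cost is a greater risk of an inconclusive trial. A reader might infer a raised risk of falsely claiming non-inferiority, but below 40% a fixed 1.478 is the stricter limit on the absolute scale: about 11.0 points at a 30% control risk and 8.1 at 20%. At event rates above 40% power rises.

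These results assume a true HR of 1, 10% drop-out, exponential event times and an unstratified approximation. All but the last are the protocol's own planning assumptions.

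**What to change.** Amend 11.4.4 before the look at 70% of the sample. State that the re-estimation holds the critical HR at 1.478, the value used for the decision, and targets about 206 first events. Define N as 206 divided by the blinded pooled probability of an observed first event per randomised patient, with drop-out included. This gives about 616-653 at a 35% event rate, 719-762 at 30% and 864-914 at 25%. Dividing by the bare 6-month event rate would be too low: 206 / 0.25 = 824, against 864-914.

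State also that, if the resulting N cannot be recruited, the power actually available will be reported.

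The cost is a short amendment and a re-run of the existing simulation code with the threshold held. The drawback is that the re-estimation may then ask for more patients, which is its stated purpose. Making the change before the pooled rate is known keeps the rule from depending on the data.
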